**FIGURE 1 F1:**
[figure not shown]
Study time schedule. AMMI: Attachment Multiple Model Interview; PSI: Parental Stress Index; PPQ: Perinatal Post-Traumatic Stress Disorder Questionnaire; LIFT: Longitudinal study of preterm infants in the Pays de la Loire region of France; ASQ: Ages and Stages Questionnaires; SDQ: Strength and Difficulties Questionnaire; GSA: Global School Adaptation; WA: Weeks of Amenorrhea; AMPLIFy: AttachMent Preterm LIFy.

Eligible patients will be identified in the LIFT cohort. The information letter will be sent to parents by post before the follow-up visit at 3 years old. A study investigator then completes the inclusion process by phone (collects additional information, answers questions from the parents, and obtains their express consent). The questionnaires (PSI and PPQ) will be sent by post one month before the appointment scheduled for the visit at 3 years of age.

Visit at 3 years of age:

The standard LIFT cohort follow-up will be performed. As part of the follow-up, prior to the appointment parents will receive the ASQ questionnaire that they will complete before the appointment and return to the LIFT cohort administration department in an enclosed prepaid envelope (one month before), specifying the date on which the questionnaire was completed.

Patients will be asked to provide consent relating to image rights before the interviews are carried out. Data from the follow-up at 3 years, as planned under the LIFT cohort, will be extracted and included in the AMPLIFy study case report forms.

Additional investigations will be carried out as part of this study: collection of the completed PSI and PPQ questionnaires, the AMMI, a 30-min interview (recorded) to assess the mother’s attachment representations to her own mother, father, and spouse and the ASCT, a story-completion task with the child (filmed) in the presence of a second accompanying adult, during which the child is asked to complete five story beginnings.

Visit at 5 years:

The standard LIFT cohort follow-up will be performed. As part of this follow-up, before the parent’s appointment the ASQ, the SDQ, and GSA will be filled out by parents. Questionnaire results will be available for the consultation at 5 years.

Data from the follow-up at 5 years, planned as part of the LIFT cohort, will be extracted and included in the AMPLIFy study case report forms.

Additional investigations will be carried out as part of this study: collection of the PSI and PPQ questionnaires (if not completed during the visit at 3 years), the AMMI, a 30-min interview (recorded) with the child’s mother to assess the mother’s attachment representations to her own mother, father, and spouse and the child’s attachment representations with the ASCT.

The inclusion and participation periods will each last 2 years and the study (inclusion + participation periods) will last 4 years in total.

Sample size calculation:

As this is a pilot study exploring the attachment representations in children born very prematurely, the size of the sample to be analyzed was determined using the data in the LIFT cohort database. Data from centers participating in the study were used to determine the number of participants who were eligible for inclusion at these centers and to estimate the total number of participants eligible for the entire study. Figure 2 shows the details regarding the number of eligible patients.

**FIGURE 2 F2:**
[figure not shown]
Study flow chart.

A total of 83 children are considered as eligible for inclusion in the two centers and will be screened for study recruitment. Participation will be offered to the parents (or the legal guardians). Assuming the occurrence of a non-participation rate in the study (due to refusal or for another reason) and an incomplete data rate for an estimated total of 25% of the eligible sample, the number of children with complete analyzable data is estimated at 63 in total. This aligns with the desired sample sizes recommended for pilot studies reported in the literature (33, 34). Participation will be offered to the parents (or the legal guardians) of 83 children considered eligible for inclusion. Consistent with the exploratory nature of this pilot study, we did not perform a statistical power analysis. Power calculations are beyond the scope of a pilot study (35). We will use a confidence interval approach to interpret the results (36). After taking into account exclusion criteria, a total number of 81 children will be included in the study.

Statistical analysis design: A flow chart will be used to depict the screening and inclusion of children included in the analysis. A descriptive analysis of the characteristics of the children included in the study will be carried out.

Descriptive analyses will be presented for all of the data collected about the children included in the study, as well as the data relating to the parents. The qualitative variables will be studied in terms of frequency and percentage. Quantitative variables will be analyzed in terms of absolute scores, medians, interquartile ranges (or extreme values), averages, standard deviations, and/or 95% average confidence intervals.

For each Q-sort score derived from the ASCT (secure, deactivating, hyperactivating, and disorganized), the average of each score recorded at 3 years and again at 5 years will be used to describe children’s attachment representations within the population of children born extremely prematurely (27).

The analysis will take place on an exploratory basis by studying the factors associated with the children’s attachment representations at 3 and 5 years old. The factors associated with each Q-score will be studied using a univariate linear regression model. A separate model will be performed for each Q-score. Multivariate analyses will be also carried out on an exploratory basis (one multivariate model for each Q-score). The following different factors will be considered (37), including specifically: neurocognitive development (using the score from the GSA questionnaire as an absolute value and the score from the ASQ questionnaire expressed as a score <285 or not); behavioral development (SDQ score between 17 and 40 or not); perinatal, prenatal, and socioenvironmental factors (term of pregnancy, birth weight and length as a z-score, sex, age of the mother, gravidity, parity); comorbidity at birth (composite criterion used in the context of the LIFT follow-up: bronchopulmonary dysplasia at 36 WG, grade 3-4 intraventricular hemorrhage, periventricular leukomalacia, grade 2-3 necrotizing enterocolitis, ligature of ductus arteriosus); the socioeconomic status and level of education of the parents; the use of medically assisted reproduction; the parents’ marital status (separated or not). The following factors will also be taken into account: parental posttraumatic stress, using the score from the PPQ questionnaire (score greater than or equal to 6), and parental stress using the PSI score as an absolute value, as well as the results of the assessment for maternal attachment representations using the scores from the AMMI dimensions as absolute values. An additional analysis using mixed models will also be performed for exploratory purposes (linear models) to analyze the longitudinal aspects of the follow-up of the children included in the study. As described previously, a separate model will be performed for each Q-score.

All tests will be performed with a two-sided level of significance of 0.05.

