## Methods and Analysis

Aims:

The primary aim of this study is the description of attachment representations at 3 and 5 years of age, and their links with neurocognitive and behavioral outcomes in children born very prematurely.

The secondary aims are to test:

-The link between attachment representations at 3 and 5 years of age and perinatal and/or prenatal and socio-environmental factors in children born very prematurely.-The link between maternal attachment representations and:०children’s attachment representations at 3 and 5 years in children born very prematurely; and०neurocognitive assessment at 3 and 5 years in children born very prematurely.

Design of the study and characteristics of the participants:

This is a longitudinal, prospective, exploratory, and bi-centric study. The inclusion criteria are: singleton infants born at less than 29 weeks of gestation in the neonatal intensive care unit (NICU) of Angers and Nantes University Hospitals included in the regional monitoring network for vulnerable newborns (Loire Infant Follow-up Team, LIFT Cohort) and with a clinical evaluation planned at 3 years of age in Angers or Nantes Hospital, with an informed consent dated and signed by the parents. The exclusion criteria are: being a child with severe neurocognitive impairment or a severe autism disorder in the 2-year LIFT follow-up evaluation.

Neonatal characteristics of the cohort are presented in Table 1.

**TABLE 1 T1:** Selected baseline characteristics of the preterm children included in the cohort.

Variable	*n* (%) or mean ± sd [min; max]
Age (years) mean, sd [min; max]	31.3 ± 5.6 [20;42]
Obesity (BMI > 30), n (%)	16 (19.8)
Number of children at home, mean, sd [min; max]	1.7 ± 1.2 [1;5]
Low parents’ socioeconomic level, n (%)	17 (23.6)
Intermediate parents’ socioeconomic level, n (%)	38 (52.7)
High parents’ socioeconomic level, n (%)	17 (23.6)
Assisted Conception Medically Assisted Reproduction, n (%)	10 (12.3)
Isolated IUGR, n (%)	20 (24.7)
IUGR associated to maternal hypertensive pathology, n (%)	12 (14.8)
Threatening Premature delivery, n (%)	46 (56.8)
Antenatal corticotherapy, n (%)	73 (90.1)
- 1 dose	27 (37.0)
- 2 doses	45 (61.6)
Hypertension during pregnancy, n (%)	22 (27.2)
Magnesium sulfate, n (%)	50 (61.7)
C-section, n (%)	45 (55.6)
Male Gender, n (%)	41 (50.6)
Gestational age, mean ± sd [min;max]	26.5 ± 1.9 [24.0;28.6]
24-25	31 (38.2)
26-27	31 (38.2)
28	19 (23.5)
Birth weight (g) mean ± sd [min;max]	865.1 ± 272.7 [450;1420]

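### Centre is not named among the factors for any Q-score model in this two-centre study, and the single-factor regressions cannot contain it; a fixed centre term would be a cheap improvement.

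*Protocol article*

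**What the plan says.** The design paragraph of Methods and Analysis states: "This is a longitudinal, prospective, exploratory, and bi-centric study". Its inclusion criteria require a child "with a clinical evaluation planned at 3 years of age in Angers or Nantes Hospital".

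The statistical analysis design paragraph, which follows Figure 2, plans three kinds of model for each ASCT Q-score:

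- Single-factor models: "The factors associated with each Q-score will be studied using a univariate linear regression model".
- Multivariate models: "Multivariate analyses will be also carried out on an exploratory basis (one multivariate model for each Q-score"). The candidates are introduced by "The following different factors will be considered (37), including specifically" and set out in detail. They include "term of pregnancy, birth weight and length as a z-score, sex, age of the mother, gravidity, parity", as well as neonatal comorbidity, socioeconomic and educational level, marital status, the questionnaire scores and the AMMI dimensions.
- Mixed models: "An additional analysis using mixed models will also be performed for exploratory purposes (linear models"). Their fixed and random terms are not listed.

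Centre appears in none of these descriptions. On testing, the paragraph says: "All tests will be performed with a two-sided level of significance of 0.05". The sample size paragraph adds that results will be interpreted through confidence intervals.

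**The concern.** A regression on one factor attributes to that factor anything else that varies with it. In a two-centre study, one such thing is the centre. If the families at one centre differ from those at the other, or if the tasks are run differently, the factor and the Q-score can both shift between centres. Pooling the children then turns two centre differences into an apparent association. If the shifts go in opposite directions, pooling can hide a real one.

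The association most exposed is the one between maternal and child attachment representations, a stated secondary aim. Table 2 describes the AMMI as a semi-structured interview and the ASCT as a narrated and enacted task. The description of the 3- and 5-year visits places both at the same appointments, so exposure and outcome could share a centre's way of working. The listed case-mix factors do not capture how a task is conducted. The displacement affects the estimate and its confidence interval as well as the p-value, so interpreting by intervals does not avoid it.

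**Working it through.** **Inputs from the article.** Two centres; 83 eligible children; an allowance of 25% for non-participation and incomplete data; 63 children expected with complete data; 81 to be included; two-sided 0.05.

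**The plan's own figure.** 83 × (1 − 0.25) = 62.25, which gives 63 when rounded up. The stated 63 is reproduced. No power or effect size is stated, so there is nothing further to reproduce.

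**Inputs that have to be assumed.** The article gives neither the split of children between centres nor any difference between centres. Assume a Normal factor and a Normal Q-score, unrelated within each centre, both shifted between centres by *d* within-centre SDs in the same direction. Let *p* be the share of children in one centre.

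**Spurious correlation when centre is left out.** The covariance between the two variables comes only from centre and equals d²p(1−p). Each variable has variance 1 + d²p(1−p). Hence

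r = d²p(1−p) / (1 + d²p(1−p)).

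At p = 0.5, p(1−p) = 0.25:

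- d = 0.3: 0.0225 / 1.0225 = 0.022
- d = 0.5: 0.0625 / 1.0625 = 0.059
- d = 0.8: 0.16 / 1.16 = 0.138
- d = 1.0: 0.25 / 1.25 = 0.200

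**Rejection rate, by formula.** With the Fisher transformation, the test statistic is centred at atanh(r) × √(n − 3). For d = 1.0 and n = 63 this is 0.203 × √60 = 1.57, so the rejection rate is about P(Z > 1.96 − 1.57), or 34.9%. The same step gives 5.3%, 7.4% and 18.9% for d = 0.3, 0.5 and 0.8.

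**Rejection rate, by simulation.** 40,000 data sets per setting, no true association, no centre term:

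| Shift in both measures (SD) | n = 63, 50:50 | n = 63, 70:30 | n = 81, 50:50 |
|---|---|---|---|
| 0.3 | 5.4% | 5.2% | 5.4% |
| 0.5 | 7.3% | 6.8% | 8.0% |
| 0.8 | 19.1% | 15.3% | 23.7% |
| 1.0 | 35.8% | 27.9% | 43.8% |

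Formula and simulation agree to within one percentage point at n = 63 with an equal split.

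**With a fixed centre term.** In the same simulations the mean spurious correlation is about 0 and the rejection rate is 4.9% to 5.1% in every setting. At n = 63 the residual degrees of freedom fall from 61 to 60, and the critical t is 2.00 either way.

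**The case against.** The strongest reply is that a journal article condenses the full protocol, and that a centre covariate is the kind of detail left to a fuller document. That stands for two of the three model types. The multivariate list is open and the mixed-model terms are not given, so centre may yet be in both. It does not fully answer the point for the single-factor models, whose stated form leaves no room for centre. Even there, a univariate model omits every confounder by design, and multivariate models with many measured case-mix variables follow. The case-mix part of the point therefore bears mainly on the single-factor results.

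A reader might be tempted to infer more than the article supports:

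- *That all the associations are estimated without centre.* This is certain only for the single-factor models.
- *That the univariate regression is the main analysis.* The article does not rank it above the multivariate one, and it calls the analysis of factors exploratory.
- *That local staff administer and score both tasks.* The article does not say who does either. At the 3-year visit the interview is recorded and the story task filmed, and both instruments have their own coding systems, so shared coding is possible. Shared coding would remove a scoring difference between centres but not a difference in conduct.
- *That the centres differ.* No difference is reported, and both recruit from one regional follow-up network.

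The reach of the mechanism is also limited. The PSI, PPQ, ASQ, SDQ and GSA are questionnaires for parents or teachers, so a difference in how staff run a task does not touch them directly. The large error rates need shifts of 0.8 to 1 SD in both measures at once.

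**Conclusion.** The point holds as a suggestion. Centre is not named for any Q-score model, and the single-factor regressions cannot contain it. A shared centre shift could then pass as an association, chiefly between the AMMI and the ASCT.

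The size is unknown. It depends on assumed equal shifts in both measures, no true link within centres and an assumed centre split. With 63 children split equally, the error rate is close to nominal at 0.3 SD, modest at 0.5 SD and serious only from about 0.8 SD. A less even split lowers it; a larger sample raises it. Nothing in the documents shows that such shifts exist, and in an exploratory pilot no stated decision turns on one of these tests. The reason to act is that the protection costs almost nothing.

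**What to change.** In the statistical analysis design paragraph, or in the analysis plan if one exists:

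- name centre (Angers or Nantes) as a fixed two-level term in the multivariate and mixed models for each Q-score;
- keep the single-factor results, and report each of them also from a model with the factor and centre, giving priority to the AMMI dimensions.

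A fixed term is preferable to a random one because a variance between centres cannot be estimated well from two centres.

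The cost is one degree of freedom per model and a sentence of wording. The place of evaluation is part of the inclusion criteria, so centre is known for every child and no new data are needed.

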**Clinical categorization carried out by the LIFT referring doctor**	
Parental questionnaire Ages and Stages Questionnaire (ASQ)	Neurodevelopmental outcome is assessed with the parent-completed “Ages and Stages Questionnaire” (ASQ) (20). The ASQ assesses development in the following five areas: communication, gross motor, fine motor, problem solving and personal-social skills. The maximum overall ASQ score is 300 and a score below 185 is considered non-optimal (21).
Parental questionnaire Strengths and Difficulties Questionnaire (SDQ)	The SDQ (22) is a screening questionnaire for measuring parents’ perceptions of their child’s prosocial and problem behaviors. It includes 25 items on a three-level scale ranging from 0 (not true) to 2 (very true). The items are split into five sub-scales that each comprise five items: emotional problems, behavioral problems, hyperactivity/inattention, peer relations, and prosocial behavior. A total difficulties score (between 0 and 40) can be calculated by adding up scores on all the scales except the prosocial scale. In a normal french population, a cutoff at 17 represents the 90th percentile (23).

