**Secondary aims**	
Description of attachment representations compared to perinatal and/or prenatal and socio-environmental factors in children born very prematurely. [Time Frame: Three and five years after preterm birth]	Child’s medical history to be completed (3 to 5 years of age) AMMI (3 and 5 years) PSI (3 and 5 years) PPQ (3 years)
Description of attachment representations in children born very prematurely compared to maternal attachment representations. [Time Frame: Three and five years after preterm birth]	+ classic LIFT cohort follow-up: Clinical categorization carried out by the LIFT cohort referring doctor (3 and 5 years old)
Neuro-cognitive and behavioral assessment in children born very prematurely compared to maternal attachment representations. [Time Frame: Three and five years after preterm birth]	Parental questionnaire ASQ (3 and 5 years) Parental questionnaire SDQ (5 years) Teacher’s questionnaire GSA (5 years)

*AMMI, Attachment Multiple Model Interview; PSI, Parental Stress Index; PPQ, Perinatal Post-Traumatic Stress Disorder Questionnaire; ASQ, Ages and Stages Questionnaires; SDQ, Strength and Difficulties Questionnaire; GSA, Global School Adaptation; LIFT, Longitudinal study of preterm infants in the Pays de la Loire region of France.*

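### The ASQ is dichotomised at <285 in the statistical section, but Table 2 of the same article defines non-optimal as below 185 of 300

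*Protocol article*

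**What the plan says.** Table 2 (description of assessment tools) states for the ASQ: "The maximum overall ASQ score is 300 and a score below 185 is considered non-optimal", with a literature citation.

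The statistical analysis paragraph of Methods and Analysis lists the factors to be regressed on each ASCT Q-sort score. Under neurocognitive development it names the GSA score as an absolute value and "the score from the ASQ questionnaire expressed as a score <285 or not". No reason is given for 285, and no other part of the article gives an ASQ cut-off.

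The SDQ entry in the same list reads "behavioral development (SDQ score between 17 and 40 or not"), which matches the cut-off of 17 that Table 2 gives for that instrument.

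Table 3 schedules the ASQ at 3 and 5 years and the GSA at 5 years only. The sample size paragraph says that "the number of children with complete analyzable data is estimated at 63 in total".

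**The concern.** The same article gives two different cut-offs for one instrument. The one in Table 2 is cited and has a stated meaning. The one in the statistical section has neither, and it sits at 95% of the maximum score. An analyst who follows the statistical section would build a binary factor whose low group holds every child short of a near-maximum score. Its regression coefficient would not describe the link between attachment representations and non-optimal neurodevelopment as Table 2 defines it.

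The links between attachment representations and neurocognitive outcome belong to the primary aim. Of the neurocognitive factors named in the statistical section, the ASQ is the only questionnaire score collected at 3 years.

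**Working it through.** **Inputs from the article.** ASQ maximum 300 and non-optimal below 185 (Table 2); analysis cut-off <285 (statistical section); 63 children with complete data (sample size paragraph). As a check on the last figure, 83 × (1 − 0.25) = 62.25, which agrees with the stated 63 to within one child.

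**Position on the scale.**
- 285/300 = 95.0%. A child who loses more than 300 − 285 = 15 points is in the low group of the analysis factor.
- 185/300 = 61.7%. A child must lose more than 300 − 185 = 115 points to be non-optimal under Table 2.
- The gap is 285 − 185 = 100 points, or one third of the scale. Every score from 185 up to just under 285 is classified differently by the two rules.

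**Illustration of the size.** The article gives no ASQ mean, SD or percentile, so any distribution is an assumption. I used a normal distribution with location m and SD parameter s, truncated to 0–300 because no score can exceed 300:

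P(score < c) = [Φ((c − m)/s) − Φ((0 − m)/s)] / [Φ((300 − m)/s) − Φ((0 − m)/s)]

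For m = 240 and s = 40, Φ(−6) is negligible, so:
- P(<285) = Φ(1.125)/Φ(1.5) = 0.8697/0.9332 = 0.932
- P(<185) = Φ(−1.375)/Φ(1.5) = 0.0846/0.9332 = 0.091
- Share classified differently = 0.932 − 0.091 = 0.841, or 0.841 × 63 ≈ 53 children

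Selected results over m = 200–290 and s = 20–50, including those that set the extremes:

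| m | s | Below 285 | Below 185 | Classified differently | Of 63 |
|---|---|---|---|---|---|
| 200 | 20 | 100.0% | 22.7% | 77.3% | 49 |
| 200 | 50 | 97.8% | 39.1% | 58.7% | 37 |
| 240 | 20 | 98.9% | 0.3% | 98.6% | 62 |
| 240 | 40 | 93.2% | 9.1% | 84.1% | 53 |
| 270 | 30 | 82.2% | 0.3% | 81.9% | 52 |
| 290 | 20 | 58.0% | 0.0% | 58.0% | 37 |

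Over the whole grid, 58%–100% of children fall below 285 and 0%–39% below 185. Between 58% and 99% are classified differently, which is about 37 to 62 of 63. Among children at or above 185, the share below 285 is 58%–100%.

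As a check on the distributional shape, a flat distribution over 0–300 (not a realistic one) puts 100/300 = 33% of all children between the two cut-offs. Of those at or above 185, 100/115 = 87% would still be in the low group.

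**The case against.** The best defence is that 285 may be a one-digit misprint for 185. If the data are analysed at 185, no child is misclassified. The matching SDQ cut-off makes a slip plausible, but the article does not confirm it. The factor list also carries a literature citation that cannot be checked here, so a deliberate 285 cannot be excluded. This means the request should be to reconcile the two places, not to presume the answer. The contradiction itself stands, because a reader or analyst would follow the printed figure.

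A second defence is that this is an exploratory pilot with no power analysis, and the fault lies in one covariate threshold that can be corrected from raw scores. That is true and makes the repair cheap. It does not justify a factor that conflicts with the article's own definition.

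Three stronger readings are tempting and are not supported:
- **That most normally developing children will be coded as impaired.** The statistical section defines only a binary factor and does not use that label. The proportion also depends on a distribution that the article does not give.
- **That the ASQ carries the primary aim.** The primary outcome measure is the ASCT, and its description is untouched. The links are also examined through the GSA and the SDQ.
- **That the ASQ is the only neurocognitive measure at both ages.** Table 3 also lists a clinical categorisation by the referring doctor at 3 and 5 years. Its content is not described, so it cannot be ruled out as neurodevelopmental, although the factor list does not name it.

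**Conclusion.** The ASQ threshold in the statistical section is wrong as written: it contradicts Table 2 by 100 points on a 300-point scale, and nothing in the article supports it. That conclusion needs no assumption.

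The number of children affected does rest on assumption. In every truncated normal scenario tested, the <285 group was a majority of the cohort and more than half of the children changed group between the two rules. The exact share cannot be fixed from the article.

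The consequence is confined to the ASQ factor in the regression models. It bears most on the neurocognitive links at 3 years. At 5 years the GSA, entered as an absolute score, gives a separate neurocognitive analysis that this error does not touch.

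**What to change.** Reconcile Table 2 and the statistical section. Use <185 in the factor list unless 285 is explicitly justified with its source and meaning.

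Changing the number alone may not give an informative factor. With m = 240 and s = 40, <185 flags 0.091 × 63 ≈ 6 children, and severe neurocognitive impairment at the 2-year evaluation is already an exclusion criterion. The total ASQ score should therefore also be entered as a continuous factor, as is planned for the GSA, PSI and AMMI scores. The resolution of the contradiction does not depend on this addition.

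The cost is one line of text and one extra or replaced form of a covariate. No new data are needed, because both forms come from the same total score.

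### SDQ and ASQ totals enter the models as yes/no factors although the numeric scores are collected, which costs at least about a third of their information on the primary aim's links

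*Protocol article*

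**What the plan says.** The Aims section makes the links between attachment representations and neurocognitive and behavioural outcomes part of the primary aim. The Statistical analysis design section fits a linear regression for each ASCT Q-score and lists the candidate factors with their coding:

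- **Binary:** ASQ (below 285 or not), SDQ ("behavioral development (SDQ score between 17 and 40 or not") and PPQ (6 or more).
- **Numeric:** GSA, PSI and the AMMI dimensions.

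No reason is given for the difference. Table 2 gives a total for each dichotomised instrument: ASQ up to 300, SDQ difficulties 0 to 40, PPQ 0 to 42. For SDQ it adds that in a normal French population "a cutoff at 17 represents the 90th percentile".

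On size and interpretation, the Sample size calculation section states that "the number of children with complete analyzable data is estimated at 63 in total", that "we did not perform a statistical power analysis", and then: "We will use a confidence interval approach to interpret the results". The analysis section closes with: "All tests will be performed with a two-sided level of significance of 0.05".

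**The concern.** A cut treats all children on the same side of it as identical. A child scoring 16 on the SDQ is grouped with a child scoring 2, and a child scoring 17 with one scoring 35. In a linear model this widens the interval around any association, and the result then depends on where the cut lies.

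This matters most for the two scores that serve the primary aim. SDQ is the only factor labelled as behavioural development. By Table 3, SDQ and GSA are collected at 5 years only, so ASQ is the only neurocognitive or behavioural score among the listed factors that is measured at 3 years. Models at that age therefore have no continuous developmental measure from the same visit.

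The pool of eligible children is fixed and small, so precision lost through coding cannot be recovered by recruiting more.

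**Working it through.** **The plan's own figure.** "A total of 83 children are considered as eligible for inclusion in the two centers", less "an incomplete data rate for an estimated total of 25% of the eligible sample": 83 × (1 − 0.25) = 62.25, rounded up to 63. The stated number reproduces. No power or effect size is stated, so there is no power figure to check.

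**Method.** Let a share p of children lie on one side of the cut. For a normal score linearly related to the outcome, the fraction of information kept is

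E = φ(z_p)² / [p(1 − p)],

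where φ is the standard normal density and z_p the normal quantile at p. The standard error for the underlying association, and so the interval width, is multiplied by about 1/√E.

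Two cases worked through:

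- 50/50: φ(0)² = 0.3989² = 0.159; divided by 0.25 gives E = 0.637.
- 10/90: φ(1.2816)² = 0.1755² = 0.0308; divided by 0.09 gives E = 0.342.

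| Share beyond the cut | Children of 63 | Kept (E) | Lost | Effective N (63 × E) | Interval width (1/√E) |
|---|---|---|---|---|---|
| 50% | 31.5 | 0.637 | 36% | 40.1 | 1.25 |
| 30% | 18.9 | 0.576 | 42% | 36.3 | 1.32 |
| 20% | 12.6 | 0.490 | 51% | 30.9 | 1.43 |
| 10% | 6.3 | 0.342 | 66% | 21.6 | 1.71 |
| 5% | 3.2 | 0.224 | 78% | 14.1 | 2.11 |

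Under these assumptions the median split is the most favourable, so 36% is the least that can be lost.

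**Which rows apply.**

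- *SDQ.* The 10% row follows if these children exceed 17 at the rate of the reference population in Table 2. The 20% and 30% rows are assumptions for a cohort at higher behavioural risk.
- *ASQ.* The documents do not say how many children fall below 285 on a 300-point scale, so no row can be assigned. Only the 36% minimum applies.

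**Consistency of the cuts.** Set side by side, the cut-offs do not agree within the protocol. The ASQ is split at 285 in the analysis section, while Table 2 calls a score below 185 non-optimal. The PPQ is split at 6 or more in the analysis section, while Table 2 treats a score above 6 as high risk. Each pair must be reconciled. With continuous coding, none of these values would affect the models.

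**The case against.** **Clinical thresholds have a rationale.** Table 2 cites thresholds for these instruments, and a contrast at a recognised threshold is easy to read. It gives none for PSI or AMMI, which explains part of the mixed coding. It does not explain all of it: Table 2 also gives a GSA threshold (above 45), yet GSA enters as a number.

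**Some developmental and behavioural information stays continuous.** This stands. Eight of the 20 GSA items concern classroom behaviour, and the PSI Child Domain covers hyperactivity, demandingness and mood. The links at 5 years are weakened, not lost.

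**The study is an exploratory pilot without a power target.** This also stands, and it limits what can be claimed. A reader might infer a specific loss of power: for an assumed true correlation of 0.35 and 63 children, a Fisher z calculation gives 81% with continuous coding and 36% at a 10/90 split. The documents give no effect size, and 0.35 is almost exactly the correlation detectable with 80% power at this size (0.347), so the 81% reflects that choice. The cost is better stated as interval width, because intervals are the protocol's declared basis for interpretation.

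**The two-thirds figure could be read too widely.** A reader might apply it to all three instruments, treat it as an upper limit, or expect only about six children above the SDQ cut. The documents support none of these. The 10% share is documented for SDQ alone, and in a reference population. No split is given for ASQ or PPQ, and a more uneven split than 10/90 would lose more.

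**PPQ is not part of the primary aim.** It measures parental post-traumatic stress, and Table 3 lists it under the secondary aims.

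**Conclusion.** The point holds for SDQ and ASQ as a matter of precision on the primary aim's links. Dichotomising loses at least 36% of the information in each score. For SDQ the loss is about 66% if the reference-population share applies, and about 42–51% if 20–30% of the cohort exceed the cut. Intervals for the underlying association are then about 1.25 times (50/50) to 1.7 times (10/90) as wide.

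These sizes assume a roughly normal score and a linear relation; an association present mainly beyond the clinical threshold would change them. The cohort's SDQ and ASQ distributions are unknown. The same coding weakness affects PPQ, but only for secondary aims. The coding does not invalidate the study: it is an avoidable loss in a small exploratory cohort, and worth correcting because correction is nearly free.

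**What to change.** In the Statistical analysis design section, and in the analysis plan if separate, enter SDQ total difficulties and the ASQ total as continuous factors in the univariate and multivariable models for each Q-score, and in the mixed models where these factors are used. Keep the clinical cut-offs as a secondary or descriptive presentation, after reconciling the two ASQ values.

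Treat PPQ the same way once its scoring is clarified: Table 2 describes 14 yes/no items but a range of 0 to 42, and one point per yes would give at most 14.

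The cost is wording only. The totals are already collected, so families and sites have no added burden. The drawback is that continuous entry assumes a linear relation, which can be checked with residual plots or a curvature term, and that the coefficients are less directly tied to clinical thresholds.
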